#### Secondary outcome measures

4.3.2

Patient Health Questionnaire-9 (PHQ-9): The Chinese version of PHQ-9 has been translated and validated, demonstrating good validity and reliability for assessing depression severity among Chinese populations (42). It consists of nine items representing various aspects of depressive symptoms with high reliability and easy to understand. Each item is rated on a four-point scale, with the patient choosing the most compatible answer based on how they felt over a two-week period. 0: no problem at all; 1: a few days; 2: most of the time; 3: every day. The total score ranges from 0 to 27, with higher scores indicating more severe depressive symptoms. Score 0 to 4: no or minimal depressive symptoms; 5 to 9: mild depression; 10 to 14: moderate depression; 15 to 19: moderately severe depression; 20 to 27: severe depression.Hospital Anxiety and Depression Scale: We will use the translated and validated Chinese version of the HADS. This version has demonstrated good validity and reliability in studies involving Chinese populations (43). The self-report scale is widely used to assess patients’ levels of anxiety and depression in healthcare settings. The scale was developed by Zigmond and Snaith in 1983 and is primarily designed to be used as a quick and easy measure of a patient’s psychological state under the guidance of a non-psychological professional (44). The HADS consists of 14 items, of which 7 items are used to assess depression (Items #2, 4, 6, 8, 10, 12, and 14 items) and 7 items of the scale are used to assess anxiety (Items #1, 3, 5, 7, 9, 11, and 13). Each item has a 4-point scale, with each item scored on a scale ranging from 0 to 3, and the total score ranging from 0 to 21.Mini-Mental State Examination (MMSE): We will use the translated and validated Chinese version of the MMSE. This version has been widely applied in various studies and has proven effective and reliable for assessing cognitive function in Chinese populations (45). The MMSE is a simple instrument widely used for the assessment of cognitive functioning and consists of 30 items with a total score of 30 points. It includes attention and calculation ability (5 points), memory (3 points), orientation (10 points), language (8 points), and executive function (4 points). 0-9: moderate cognitive disorder; 10-17: mild cognitive disorder; 18-23: mild cognitive impairment; and 24-30: normal cognitive level.Pittsburgh sleep quality index (PSQI): We will use the Chinese translated version of the PSQI. The translated version has been validated and shown to be effective and reliable in assessing sleep quality among Chinese populations (46). The main purpose of the PSQI is to comprehensively assess the quality of an individual’s sleep, including sleep duration, difficulty falling asleep, sleep effect, sleep depth, number of sleep awakenings, and sleep medication use (47). It contains 7 main subscales that assess different aspects of sleep: subjective sleep quality, difficulty falling asleep, sleep duration, sleep effect, sleep depth, use of medications, and daytime dysfunction. Each subscale has a score range of 0-3 and a total score of 21, with higher scores representing poorer sleep quality. a total PSQI score of >5 is usually considered poor sleep quality.Stroke Specific Quality of Life Scale (SS-QOL): We will use the translated and validated Chinese version of the SS-QOL. This version has demonstrated good validity and reliability for assessing the quality of life in Chinese stroke patients (48). The scale includes 12 dimensions of energy, family role, language, activity, mood, personality, self-care, social role, thinking, upper limb function, vision, and work/productivity, with each entry on a 5-point scale (1 to 5). The total score ranged from 49 to 245, with higher scores indicating better quality of life.A 32-channel wireless multichannel EEG acquisition and analysis system from Xi’an ZhenTec Intelligence Technology, ZhenTec NT1, will be used for brain EEG data acquisition. Saline electrodes will be used and placed according to the international standard lead 10-20 electrode system position. The sampling rate will be 1000 Hz and electrode impedance will be kept below 10 kΩ. Resting state EEG will be recorded from the patients before and after four weeks of intervention. Resting-state EEG: EEG data will be recorded for 5 minutes in a quiet state. LZC complexity nonlinear feature extraction will be performed for the full frequency band (0.6-46Hz), δ (1-3.5Hz), θ (4-7Hz), α (8-13Hz), and β (13-30Hz) frequency bands of the resting-state EEG, respectively, to calculate the LZC values.A 64-channel fNIRS device (BS-2000L, Wuhan Znion Technology Co., Ltd., China) will be used to collect information on changes in oxygenated hemoglobin (HbO) and deoxyhemoglobin (HbR) concentrations in the prefrontal lobe and part of the temporal lobe of the subjects during the VFT task. The VFT consists of the following components: (1)A 30-second pre-task baseline period to establish a resting state, during which participants will be asked to repeat the sequence “12345” to ensure consistent starting conditions. (2)A 60-second task period divided into three 20-second segments, during which participants are asked to generate as many words as possible starting with given syllables (e.g., “ba,” “da,” “pa”). (3)A 70-second post-task baseline period during which participants will again repeat the sequence “12345” until the end of the assessment at 170 seconds. This task evaluates regional brain activity and forebrain functional network connectivity. Data preprocessing includes artifact removal and baseline correction using the moving average method. HbO and HbR integral values will be calculated by averaging data from all channels, representing the hemodynamic response during the task period.

### Participant timeline

4.4

The schedule for the study is shown in **Table 1**.

**Table 1 T1:** Participant timeline.

[figure not shown]	

### Sample size and feasibility criteria

4.5

Since this study employs a novel mixed herbal aromatherapy intervention, there is no prior research directly comparable to reference. As this is a pilot RCT, the focus is on assessing the feasibility of the intervention rather than hypothesis testing. Therefore, the sample size estimation is not based on power analysis but according to rule of thumb.

Based on the guidance from Billingham et al. (49), a sample size of approximately 30 participants per group is considered appropriate for a pilot study. This sample size is justified by the need to gather preliminary data on feasibility outcomes, such as recruitment rates, adherence rates, and completion rates, and to ensure sufficient variability and precision in the estimates.

Taking into account 10% potential dropout rates, we will aim to recruit approximately 33 participants per group to ensure we have enough data for the feasibility analysis. This will result in a total sample size of approximately 99 participants across the three groups.

The predefined criteria for feasibility outcomes are:

- Recruitment rate of at least 70%: This is considered a reasonable and achievable target for pilot studies to ensure adequate participant recruitment.

- Adherence rate of at least 80%: This reflects a high level of participant engagement and compliance with the intervention protocol, which is crucial for obtaining reliable data.

- Completion rate of at least 85%: This indicates that the majority of participants complete the study, ensuring data integrity and minimizing the impact of dropouts on the study results.

These criteria will help determine the feasibility of conducting a full-scale RCT.

### Recruitment

4.6

All participants will be recruited at the Second Rehabilitation Hospital of Shanghai, where research advertisements will be posted to attract participants. To ensure the quality of recruitment, the chief investigator will oversee the review of medical records. The recruitment process will be conducted by two dedicated researchers, who will meticulously document the participants’ medical histories, both past and present.

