#### Primary outcome measures

4.3.1

1. Recruitment rates: Recruitment rates will be calculated as the proportion of successfully recruited eligible participants within the specified period, documented weekly, and reported as a percentage of the total planned recruitment. A recruitment rate of at least 70% will be considered acceptable.

2. Intervention adherence: Intervention adherence will measure the proportion of participants who complete the intervention as planned. This will be tracked using participant logs that record the completion of each aromatherapy session, CBT session, and conventional treatment session. Adherence to each component will be reported weekly. An adherence rate of at least 80% will be considered acceptable. Additionally, feasibility outcomes will include the proportion of participants who complete all assessments as scheduled, assessing the practicality of integrating aromatherapy with existing treatments.

3. Assessment completion: Assessment completion will assess the proportion of participants who complete all scheduled assessments and follow-ups. This will be calculated and reported at the end of the intervention. A completion rate of at least 85% will be considered acceptable.

5. Safety Assessment: Safety will be evaluated through subjective and objective measures. Participants will report any discomfort or adverse reactions, and vital signs (heart rate, respiratory rate, blood pressure) will be monitored before and after each session. An adverse event log will document all incidents and management actions. Adverse reactions will be categorized as mild, moderate, or severe.

- Moderate: Noticeable symptoms that may interfere with daily activities but are not life-threatening, requiring medical intervention or short-term observation.

- Severe: Symptoms significantly impacting daily life, potentially life-threatening, requiring intensive medical intervention such as hospitalization or emergency medication.

An acceptable safety threshold is set at no more than 10% of participants experiencing moderate to severe adverse reactions.

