### Implementation

5.3

An independent statistician, separate from the participant enrollment and intervention administration processes, will generate the allocation sequence using Research Randomizer software (https://www.randomizer.org/), ensuring a balanced 1:1:1allocation to control group, CBT group or aromatherapy group. Trained research staff will manage participant enrollment, screening for eligibility without access to the allocation sequence, thus remaining uninformed of group assignments. Following consent, a distinct research team member will access the allocation via a secure system to assign participants to interventions, communicating these assignments to the intervention administrator responsible for treatment delivery. This administrator will be excluded from the enrolment and outcome assessment processes to avoid potential biases.

CBT will be delivered by the hospital unit’s psychotherapists. The aromatherapy intervention, utilizing traditional Chinese herbal powders, will be administered by physicians from the TCM Rehabilitation Department. These physicians have received specialized training in herbal powder aromatherapy, which includes:

Fundamentals of Aromatherapy: Understanding the principles and therapeutic benefits of aromatherapy using Chinese herbal powders.Application Techniques: Hands-on training on the proper preparation and application of herbal powders for aromatherapy.Safety Protocols: Comprehensive instruction on safety measures to prevent adverse reactions and ensure patient safety during the treatment.Patient Interaction: Techniques for effectively communicating with patients to enhance their comfort and cooperation during the therapy.

The training program is conducted by senior TCM specialists and certified aromatherapists, ensuring that the physicians are proficient in delivering the intervention effectively and safely. During the aromatherapy sessions, these trained physicians will accompany patients throughout the treatment to ensure proper and safe application.

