#### Primary outcome analysis: feasibility metrics

8.1.1

Recruitment, adherence, and completion rates will be the focus, analyzed descriptively to provide insights into the practical implementation and scalability of the intervention. Each metric will be reported as a percentage:

- Recruitment rate: Proportion of eligible participants who were successfully recruited.

- Intervention adherence: Proportion of participants who adhered to the intervention throughout the study.

- Assessment completion: Proportion of participants who completed all assessments and follow-ups.

- Safety assessment: Safety will be evaluated through subjective and objective measures, including monitoring vital signs and documenting adverse reactions.

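### The recruitment rate as written may not measure uptake among eligible inpatients with post-stroke depression, so its 70% criterion can pass while uptake is well below 70%

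*Protocol article*

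**What the plan says.** Section 4.6 (Recruitment) says that all participants come from one rehabilitation hospital, "where research advertisements will be posted to attract participants". As a quality measure it adds that "the chief investigator will oversee the review of medical records", and it gives recruitment to two dedicated researchers. It does not say whose records are reviewed, or whether the review finds candidates or only checks them.

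Section 5.3 (Implementation) says: "Trained research staff will manage participant enrollment, screening for eligibility without access to the allocation sequence". The pool to be screened is not defined.

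The rate is defined in two ways:

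- Section 4.3.1 opens with an eligible-patient wording: "Recruitment rates will be calculated as the proportion of successfully recruited eligible participants within the specified period". The count is kept week by week, but the denominator then changes, since the result is to be "reported as a percentage of the total planned recruitment". The threshold follows: "A recruitment rate of at least 70% will be considered acceptable".
- Section 8.1.1: "Proportion of eligible participants who were successfully recruited".

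Section 4.5 repeats the threshold without naming a denominator: "Recruitment rate of at least 70%: This is considered a reasonable and achievable target for pilot studies to ensure adequate participant recruitment". The same section says that the feasibility criteria will help decide whether a full-scale trial is feasible. Section 4.2.2.3 states that all patients are inpatients.

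**The concern.** Recruitment is a primary outcome and one of the criteria for going on to a full-scale trial. For that decision the useful quantity is how many of the hospital's eligible patients will join when invited. An advertisement reaches those who notice it and choose to answer. An eligible inpatient who does not answer enters the count only if someone identifies that patient by another route, and the article describes none.

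If the eligible pool is made up of responders, the rate in section 8.1.1 is a conversion rate among people who have already shown interest. If the rate is taken against the plan, as in section 4.3.1, it measures accrual against a target and carries no information about how many were eligible. In neither case does a pass at 70% show that 70% of eligible inpatients can be enrolled.

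**Working it through.** **Planned recruitment.** Section 4.5 starts from about 30 per group and allows 10% for dropout. 30 × 1.1 = 33 per group, and 33 × 3 = 99, which reproduces the stated total. (Dividing by 0.9 gives 33.3 per group; the article says approximately, and nothing here turns on the difference.)

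**Rate against the plan (section 4.3.1).** Rate = recruited / 99.

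- 70 / 99 = 70.7%, a pass. 69 / 99 = 69.7%, a fail.
- The number of eligible inpatients does not enter. Uptake is recruited / eligible. The eligible counts below are assumptions, since the article gives none.

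| Recruited | Eligible inpatients (assumed) | Rate against plan | Uptake among eligible |
|---|---|---|---|
| 70 | 100 | 70.7%, pass | 70.0% |
| 70 | 200 | 70.7%, pass | 35.0% |
| 70 | 300 | 70.7%, pass | 23.3% |
| 70 | 400 | 70.7%, pass | 17.5% |

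**Rate among eligible participants (section 8.1.1).** The result depends on who is counted as eligible.

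*If all eligible inpatients are counted from records*, the rate is the uptake, and a pass means at least 70% uptake. There is no gap.

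*If only advertisement responders are counted*, then

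uptake among all eligible = share of eligible inpatients who respond × share of responders who enrol.

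Both shares are assumptions.

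| Responders who enrol = reported rate | Uptake if 30% respond | Uptake if 60% respond | Response share at which uptake reaches 70% |
|---|---|---|---|
| 80%, pass | 0.30 × 0.80 = 24% | 0.60 × 0.80 = 48% | 0.70 / 0.80 = 87.5% |
| 90%, pass | 0.30 × 0.90 = 27% | 0.60 × 0.90 = 54% | 0.70 / 0.90 = 77.8% |
| 95%, pass | 0.30 × 0.95 = 28.5% | 0.60 × 0.95 = 57% | 0.70 / 0.95 = 73.7% |

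The last column matters because the 30% to 60% range contains only cases where uptake falls short. At 90% enrolment, a response share of about 78% or more brings true uptake to 70% as well.

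**The two definitions can disagree.** If 99 are recruited from an assumed 300 eligible, the rate is 99 / 99 = 100% against the plan and 99 / 300 = 33% among eligible. If 40 are recruited from an assumed 50 eligible, it is 40 / 99 = 40.4% against the plan and 40 / 50 = 80% among eligible.

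**The case against.** A reader might infer from the advertisements that the rate counts only volunteers and that non-responders are never identified. The documents do not support this as fact. Section 8.1.1 does not restrict eligible participants to responders. Section 4.6 mentions a review of medical records straight after the advertisements, and that review could be how cases are found. Section 5.3 provides for eligibility screening without saying who is screened. Section 4.1.2 gives eligible patients time with the information sheet before consent, so eligibility is judged before enrolment. The text leaves the pool open. This part of the objection stands, and the point is therefore that the rate may not measure uptake.

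It is also fair that, under section 4.3.1, advertising has no influence on the denominator, which is the planned 99. A pass with low uptake is then a consequence of dividing by the plan, and the recruitment route is not its cause. This stands too, but it does not rescue the criterion, because that definition does not measure uptake at all. Weekly accrual is still useful for planning a trial that recruits in the same way.

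Lastly, an article condenses a fuller protocol, and a screening log may be described there. Its absence here is not counted as a fault. What remains is in the article itself: a recruitment route and two definitions of a primary outcome, none of which ensures that uptake among eligible inpatients is what the 70% is applied to. Choosing the section 8.1.1 definition over the other would not be enough on its own, because the eligible pool would still be undefined.

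**Conclusion.** The point holds in a limited form. Neither stated definition ensures that uptake among eligible inpatients with post-stroke depression is measured, and under each the 70% criterion can pass while that uptake is well below 70%. Under section 4.3.1 this follows from the denominator alone. Under section 8.1.1 it holds only if the eligible pool consists of responders, which the text allows but does not state.

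The size cannot be known, because the article gives no count of eligible inpatients or responders. The illustrative gap, 90% reported against 27% to 54% uptake, rests on the assumed shares and disappears at high response.

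A reader might also infer that self-selected volunteers would raise the adherence rate. Nothing in the article gives a figure or statement on that, and it forms no part of this conclusion.

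**What to change.** In section 4.6, state that the two recruiters use the planned record review to screen stroke inpatients consecutively throughout the recruitment period, log everyone who meets the criteria other than consent, and approach them. Consent has to be set aside for this purpose because section 4.1.1.1 lists it as an inclusion criterion; read literally, that would remove everyone who declines from the denominator.

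In sections 4.3.1, 4.5 and 8.1.1, use one definition: the 70% criterion applies to enrolled patients divided by those in the log. Report recruitment against the planned 99, and the rate among advertisement responders, separately and descriptively.

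If the record review is already meant to find cases, one sentence in section 4.6 saying so settles that part, and only the denominator remains to be aligned.

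The trial is in a single hospital, all patients are inpatients, and the recruiters and a record review are already planned, so the change is practicable. It costs some extra screening work, more if the present review covers only responders, and the reported rate will probably be lower.

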## Assignment of interventions: allocation

5

### Sequence generation

5.1

Participants will be randomized in a 1:1:1 ratio to control group, CBT group or aromatherapy group. Due to the unique characteristics of each intervention, complete blinding of participants and therapists is not possible. However, measures will be taken to minimize bias, including withholding specific hypotheses about the interventions from participants. Data collection will be performed by investigators blinded to group assignments. Furthermore, data analysis will occur under blinded conditions, with assignments coded and concealed until the conclusion of the analysis.

### Concealment mechanism

5.2

The allocation sequence will be implemented through a centralized, web-based service provided by Research Randomizer (https://www.randomizer.org/). An independent team member, uninvolved in participant enrollment or intervention assignment, will conduct the randomization to ensure the sequence’s concealment. Group assignments will then be relayed to the team administering the interventions, safeguarding against any prior knowledge of participant assignments by the enrolment and intervention teams. This strategy guarantees the sequence’s concealment until assignment, maintaining allocation concealment. Additionally, researchers collecting data will be blinded to assignments, reducing bias. The coding and concealment of group assignments will be maintained until the analysis phase is completed.

### Implementation

5.3

An independent statistician, separate from the participant enrollment and intervention administration processes, will generate the allocation sequence using Research Randomizer software (https://www.randomizer.org/), ensuring a balanced 1:1:1allocation to control group, CBT group or aromatherapy group. Trained research staff will manage participant enrollment, screening for eligibility without access to the allocation sequence, thus remaining uninformed of group assignments. Following consent, a distinct research team member will access the allocation via a secure system to assign participants to interventions, communicating these assignments to the intervention administrator responsible for treatment delivery. This administrator will be excluded from the enrolment and outcome assessment processes to avoid potential biases.

CBT will be delivered by the hospital unit’s psychotherapists. The aromatherapy intervention, utilizing traditional Chinese herbal powders, will be administered by physicians from the TCM Rehabilitation Department. These physicians have received specialized training in herbal powder aromatherapy, which includes:

Fundamentals of Aromatherapy: Understanding the principles and therapeutic benefits of aromatherapy using Chinese herbal powders.Application Techniques: Hands-on training on the proper preparation and application of herbal powders for aromatherapy.Safety Protocols: Comprehensive instruction on safety measures to prevent adverse reactions and ensure patient safety during the treatment.Patient Interaction: Techniques for effectively communicating with patients to enhance their comfort and cooperation during the therapy.

The training program is conducted by senior TCM specialists and certified aromatherapists, ensuring that the physicians are proficient in delivering the intervention effectively and safely. During the aromatherapy sessions, these trained physicians will accompany patients throughout the treatment to ensure proper and safe application.

